##### Improvement in knee pain at 4, 8, 12, 16, and 20 weeks

Change in knee pain, measured by a 100mm VAS and the proportion of participants improving by the minimum clinically important difference (15mm) [39] at weeks 4, 8, 12, 16, and 20 are secondary outcomes.

##### Change in pain, function, and stiffness over 24 weeks

WOMAC (Western Ontario and McMasters Universities Osteoarthritis Index [40]) is a widely used instrument in OA research and recommended by OARSI [27] which assesses knee pain, function and stiffness. Improvements in WOMAC knee pain, function, and stiffness will be assessed over 24 weeks.

##### OMERACT-OARSI responder criteria

A simplified set of responder criteria focused on pain, function and patient global assessment developed by OMERACT (Outcome measures in Rheumatology)-OARSI will be assessed at all time-points [41].

##### Co-pathology present on MRI

Bone marrow lesions (BMLs) defined as an ill-defined hyperintensity in the subchondral bone, on MRI will be assessed on the sagittal T2 weighted sequences at the medial tibial, medial femoral, lateral tibial, lateral femoral and patella sites by means of image processing on commercial in-house imaging software. The maximum size of each lesion will be measured in mm^2^ using software cursors applied to the greatest area of the lesion, as previously described [32]. Previously we have demonstrated an ICC of 0.84 to 0.91 [32], using this method. Total BML size (mm^2^) will be calculated as the sum of every lesion within the medial tibial, medial femoral, lateral tibial, lateral femoral and patella sites at screening and 24 weeks.

Cartilage defects will be assessed at the medial tibial, medial femoral, lateral tibial, lateral femoral and patella sites using modified Outerbridge classification system, as we have previously described [42]: grade 0 = normal cartilage; grade 1 = focal blistering and intra-cartilaginous low-signal intensity area with an intact surface and base; grade 2 = irregularities on the surface or base and loss of thickness <50%; grade 3 = deep ulceration with loss of thickness >50%; and grade 4 = full-thickness chondral wear with exposure of subchondral bone. In our previous study, we demonstrated the ICCs ranged from 0.80 to 0.95 [42] for the different knee sites, using this method.

Meniscal extrusion will be assessed as we have previously described [43] as the proportion of the menisci affected by a partial or full extrusion at the anterior, middle, and posterior horns (medially/laterally). In our previous study we demonstrated the intra- and inter-reader ICCs ranged from 0.85 to 0.92 for meniscal extrusion [44].

##### Lower limb muscle strength

Lower limb muscle strength is a key correlate of pain and tends to increase when pain is reduced [45]. We will assess leg strength by dynamometry at the lower limb (involving both legs simultaneously) at weeks 0, 12 and 24. The muscles measured in this technique are mainly the quadriceps and hip flexors. The previously published repeatability estimate (Cronbach’s α) for this method is 0.91 [46]. This measure will be omitted at Telehealth appointments.

##### Knee surgery and joint injections

Whether the participant undergoes any knee surgery (including arthroscopies or joint replacement surgery) or injectable treatment during the trial, will be assessed by questionnaire at each time point. Study participants will also be asked to provide consent to have their data linked to the Australian Orthopaedic Association National Joint Replacement Registry (AOANJRR). *Any data linkage that occurs as part of this study will be subject to conditions around data security and privacy for our participants. The data that we receive from other databases will only be used for the purposes outlined in our study protocol.*

##### Concomitant medication use

Medication usage (including prescription, over-the-counter, and natural/herbal remedies) will be documented at each clinic visit (screening, baseline, 12 and 24 weeks). Participants will be asked to keep analgesic medications as stable as possible but if there are changes to the medications used or dose changes during the trial the reason will be documented.

##### Health economics outcomes

Health state utility, resource utilisation and costs will be measured throughout the study. Health state utility values (HSUV) will be assessed using The Assessment of Quality of Life (AQoL-8D) [47] and the 5-level EuroQoL-5 dimensional version (EQ-5D-5L) [48] at baseline, weeks 12 and 24. OA-related health service use will be assessed at baseline and week 24. This will include visits to primary care physicians, medical specialists, and physiotherapists; medical imaging, procedures, tests and investigations for knee pain; hospital admissions and attendances for knee pain, and use of community services related to knee pain. Patient incurred costs for transport and specialised equipment purchased/hired due to knee pain will also be collected. For services subsidised by Medicare, costs will be taken from the Medicare Benefits Schedule; patient out-of-pocket costs will be self-reported.

Indirect costs will include absenteeism and presenteeism due to knee pain. Participants will be asked about their concession, health care card & private health insurance status as costs vary based on these.

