Diacerein is a semisynthetic anthraquinone derivative that blocks IL-1β, and in vitro, also stimulates the production of cartilage growth factors such as transforming growth factor β [17]. In animal models of OA, diacerein significantly reduced cartilage degradation compared with untreated animals [18, 19]. In humans, the few acceptable-quality trials show inconsistent results concerning the effect of diacerein in OA. The pooled results from the latest systematic review of 10 trials showed that diacerein had a small beneficial effect on pain and joint space narrowing (JSN) [20], but the quality of evidence was low. Apart from their relatively low quality, another limitation of existing trials is that they include patients with knee OA regardless of whether they had an inflammatory phenotype. As diacerein targets inflammation, it may be that its effects will be greater and more definitive if its use is targeted to patients with signs of inflammatory OA.

Recommendations for the use of diacerein for OA treatment are inconsistent. Although the European League Against Rheumatism (EULAR) [21]) has recommended diacerein as a treatment option for OA, updated international guidelines from the Osteoarthritis Research Society International (OARSI) [22] and the American College of Rheumatology (ACR) [23] recommend against its use, in part because of concerns regarding adverse events, most notably diarrhoea. However, both the European Medicines Agency (EMA’s) Pharmacovigilance and Risk Assessment Committee (PRAC) [24] and the European Society for Clinical and Economic Aspects of Osteoporosis and Osteoarthritis (ESCEO) [25] have evaluated the efficacy and safety of diacerein and concluded that the benefit of diacerein outweighs its known risks for OA treatment. A chief investigator on the present study also performed a review and concluded that diacerein is safe, has a modest effect on pain, and is a worthwhile treatment option for OA [13]. Thus, the use of diacerein for OA treatment should not be ruled out due to safety issues.

Therefore, we aim to conduct a multi-centre, randomised, double-blind, placebo-controlled trial, to determine the effect of diacerein on knee pain and effusion-synovitis over 24 weeks in patients with clinical knee OA, significant knee pain, and MRI-detected effusion synovitis.

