### Intervention

The treatment dose for this trial is diacerein 50 mg twice daily, as this is the recommended therapeutic dose for this drug. Eligible patients will start the trial taking one capsule daily with food, containing 50 mg of diacerein or identical placebo, for the first 2 weeks. This will then be increased to two capsules daily with food, equating to 100 mg of diacerein or identical placebo, to be taken for the remainder of the 24-week trial. The gradual increase in dose, as recommended by PRAC [24], aims to reduce the side effect of loose stool and diarrhoea caused by diacerein.

At 2 weeks, study staff will contact participants by telephone to assess any potential side effects and instruct them to increase dosage if appropriate. Depending on the side-effect profile participants report during the trial, it is possible for participants to remain on 50 mg/day after week 2 or for participants to reduce their dose from 100 mg/day back to 50 mg/day anytime during the trial. This decision will be made in consultation with the medical doctor at each site. The reason participants can remain on half the dose is that the effect of diacerein on pain improvement does not appear to be dose-responsive. For example, the literature suggests that 50 mg/day has a similar efficacy compared to 100 mg per day (− 15.6 vs − 18.3) [36].

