### Protocol amendments

Protocol amendments include inclusion criteria, dose of intervention, and statistical analysis plan (Table 3). All these changes have been approved by the medical doctors on this study, Data and Safety Monitoring Board, steering committee, and ethics committees.

**Table 3 Tab3:** Protocol amendments

	Original protocol (version 1.3, 17 September 2018)	Updated protocol (version 1.6, 1 October 2020)	Reasons
Inclusion criteria	1. Males and females aged 40 to 64 years old. 2. Significant knee pain on most days (defined as a visual analogue scale (VAS) greater than or equal to 40mm). 3. Meet American College of Rheumatology (ACR) clinical criteria for knee osteoarthritis confirmed by a rheumatologist. 4. Any knee effusion-synovitis present on MRI. 5. Are willing to participate in the study for 6 months.	One inclusion criterion added: Participants who are screened via Telehealth must have radiographic knee osteoarthritis defined as joint space narrowing or an osteophyte present (score ≥1 on the OARSI atlas).	The protocol has been updated to accommodate Telehealth visits. This is to minimise the impact of COVID-19 on recruitment and retention. Our preference will continue to be face-to-face clinic visits; however, if this is not possible, a Telehealth option will be available. All participants screened via Telehealth will have to have osteoarthritis confirmed on an x-ray, to minimise the risk of enrolling a patient without the condition of interest.
Dose of intervention	Participants will start the trial taking one capsule daily with food, containing 50 mg of diacerein, for the first 2 weeks. This will then be increased to two capsules daily with food, equating to 100 mg of diacerein, to be taken for the remainder of the 24-week trial.	Participants will be allowed to reduce their dose from 100 mg/day to 50 mg/day anytime during the trial after consulting with the medical doctor at each site.	Some participants have experienced side effects that prohibit them from increasing their dosage at week 2. Moreover, the effect of diacerein on pain improvement does not appear to be dose-responsive. For example, the literature suggests that 50 mg/day has a similar efficacy compared to 100mg per day (− 15.6 vs − 18.3) [37].

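### Health-economics costs are limited to OA and knee pain, so most care and lost work caused by study-drug side effects is not counted

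*Protocol article*

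**What the plan says.** All references are to the protocol article.

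- **Service use** (Health economics outcomes): "OA-related health service use will be assessed at baseline and week 24". GP, specialist and physiotherapy visits come under that label with no further limit.
- **Imaging and tests:** "medical imaging, procedures, tests and investigations for knee pain".
- **Hospital and community services:** "hospital admissions and attendances for knee pain, and use of community services related to knee pain".
- **Out-of-pocket items:** "Patient incurred costs for transport and specialised equipment purchased/hired due to knee pain will also be collected".
- **Lost work:** "Indirect costs will include absenteeism and presenteeism due to knee pain".
- **Utilities:** the same section collects AQoL-8D and EQ-5D-5L at baseline, week 12 and week 24. These are general health measures with no knee-pain limit.
- **Side effects:** the Intervention section explains that the gradual dose increase "aims to reduce the side effect of loose stool and diarrhoea caused by diacerein". The Background says that two guideline bodies advise against the drug, "in part because of concerns regarding adverse events, most notably diarrhoea". Table 3 (Protocol amendments) records: "Some participants have experienced side effects that prohibit them from increasing their dosage at week 2".
- **Other relevant records:** Table 1 schedules a medication cost diary among the health-economics items, and adverse-event recording at every contact from week 2 to week 24. The Concomitant medication use section covers all types of medicine. Medicare numbers are taken for future linkage (Demographics and Medicare number).

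**The concern.** A cost comparison between a drug and placebo should count what the drug saves and what it causes. Here the saving side is open: if diacerein reduces knee pain, fewer knee-related visits, tests and lost days will show up as lower cost. The harm side is largely closed, because a stool test, an admission or a day off work for diarrhoea is neither for nor due to knee pain. The omission is not neutral between arms if, as the article itself expects, the drug causes diarrhoea.

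There is also a mismatch of scope. The utilities can fall when a participant is unwell from a side effect, whereas the cost of the same episode is mostly outside the definition. A cost-utility result built from these parts would set disease-only costs against whole-health outcomes. What is at stake is the direction of error in one secondary outcome.

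**Working it through.** The article gives no cost figure, so there is nothing to reproduce. The check is to place each cost item against a side-effect episode, then work out the direction and an assumed range.

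**Step 1: is a side-effect episode counted?**

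| Item | Stated limit | Side-effect episode counted? |
|---|---|---|
| Imaging, procedures, tests | knee pain | No |
| Admissions, attendances | knee pain | No |
| Community services | knee pain | No |
| Transport, equipment | knee pain | No |
| Absenteeism, presenteeism | knee pain | No |
| GP, specialist, physiotherapy visits | OA-related | Only if a visit for a side effect of OA treatment is read as OA-related |
| Medicines | none stated (cost diary, medication record) | Possibly, in part |

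Table 1 lists health service utilisation and days off work without a limit, but the Health economics outcomes section is where they are defined.

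**Step 2: direction.** Let K be the mean knee-related cost and S the mean side-effect cost that falls outside the definition, with subscripts D (diacerein) and P (placebo).

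- Full difference = (K_D − K_P) + (S_D − S_P)
- Counted difference = K_D − K_P
- Error = counted − full = −(S_D − S_P)

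The error is negative, making diacerein look cheaper, whenever S_D > S_P. It is zero when S_D = S_P. It would favour placebo only if side-effect costs were higher on placebo, which runs against the article's own account of the drug.

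**Step 3: range, on assumed inputs.** The documents give no excess risk, no rate of resulting service use and no unit cost. With the same cost per episode in both arms:

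S_D − S_P = excess side-effect risk × proportion leading to service use or lost work × cost per episode

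Assume an excess of 0 to 30 percentage points and a proportion of 10% to 60%. The number per arm, 130, is from Sample size calculations.

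- Excess 0: 0 episodes
- 0.05 × 0.10 = 0.005 per participant; × 130 = 0.65 episodes
- 0.15 × 0.30 = 0.045; × 130 = 5.85 episodes
- 0.30 × 0.60 = 0.18; × 130 = 23.4 episodes

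So between 0 and about 23 net episodes would go uncounted in the diacerein arm, or 0 to 0.18 of one episode's cost per participant. With no unit cost in the documents, I leave it in episodes.

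**The case against.** **No cost comparison is set out.** The Objective and Statistical analysis sections describe no between-arm cost analysis, perspective or cost total, and a fuller plan may add adverse-event costs. It is fair that the article's silence on costing adverse events is not in itself a fault. What stands is the stated scope of collection. Health economics is listed under Secondary outcome measures, and the Statistical analysis section applies intention-to-treat analysis to secondary outcomes, so following the text produces the narrower cost.

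**The lists may not be exhaustive.** They say what the costs will include. That leaves room for GP and specialist visits, as conceded above. It helps less for tests, admissions and lost work, where the knee-pain limit is attached to the item itself.

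**Other records may fill the gap.** The medication cost diary and medication record may pick up medicines bought for side effects. Medicare linkage might recover subsidised services, but it is described only as a future possibility, is not tied to this outcome and would not cover lost work. A reader might infer that all side-effect costs are left out; the article does not support that.

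**The imbalance is not demonstrated.** A reader might take Table 3 as evidence that side effects are already more frequent on diacerein. It names no arm, and the trial is blinded. The expectation of an imbalance rests on the Background and Intervention sections, not on trial data.

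**The trial's message does not depend on cost.** A reader might link this point to the Discussion, which calls the drug inexpensive and well tolerated and anticipates an effect on guidelines. That passage makes the effect on guidelines conditional on benefit for pain and effusion-synovitis, not on a cost result.

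**Disease-specific costing is a legitimate choice.** It limits noise in a trial of 260. This stands against moving to all-cause costing, which would be a trade-off rather than a correction. It does not justify omitting costs attributable to the treatment under test.

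**Conclusion.** The point holds in a limited form. As defined, the cost outcome omits tests, admissions, community services, related transport and lost work caused by study-drug side effects. It is ambiguous for GP and specialist visits and may partly capture medicines. If side effects are more frequent on diacerein, the counted cost difference errs in that drug's favour; if they are not, this error vanishes. The condition is the article's own premise, not an observed result.

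The size cannot be fixed from the documents. The range of 0 to about 23 episodes rests wholly on assumed inputs, and no total cost, cost variability or decision threshold is given against which to judge it. It may be small. A reader might infer that the economic conclusion will be wrong or that the trial's main result is compromised; neither follows. This is a minor, inexpensive improvement to one secondary outcome, and the primary pain analysis is unaffected.

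**What to change.** In Health economics outcomes, define service use and lost work as arising from knee pain or from a suspected side effect of study capsules, and record which reason applies. Use the existing baseline and week-24 form; the side-effect reason can arise only at week 24. State explicitly that GP and specialist visits for side effects are included.

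If the form can no longer be changed, attach unit costs to the visits, tests, admissions and lost days held in the adverse-event records, identically in both arms. This works only as far as those records contain such detail, so that should be checked first.

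In either case, report the knee-pain-only cost as a component of the total.

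Cost: one or two extra questionnaire items and an amendment to carry them, or some costing work on data already collected. Total costs will be somewhat more variable. Nothing changes in treatment, visits or the primary analysis.

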##### Bloods

Blood samples will be taken at screening, weeks 12 and 24 for safety and storage. The safety blood tests performed at each time point include a full blood count, urea and electrolytes test (UEC) and a liver function test. Storage of blood samples will occur at each time point for future biomarker testing. Potential biomarkers to be tested include inflammatory markers, cartilage and synovial degradation markers which have been implicated in the pathogenesis of knee OA. The blood will be stored at − 80°C.

##### Treatment guessing

At 12 and 24 weeks, participants will be asked what treatment they think they received with the following options: Active treatment (diacerein), Inactive treatment (placebo), or Not sure.

##### Adherence

At 12 and 24 weeks, participants will be asked to return all bottles (used or unused), such that adherence can be calculated based on pill counts [49]. All bottles (both returned and un-dispensed) are to be stored on site until the next Monitoring Visit. After reconciliation, returned bottles will be destroyed on-site.

#### Additional measures

##### Demographics and Medicare number

At screening we will collect information on sex and date of birth. At baseline we will record participants’ Medicare number for the purpose of future data linkage. Medicare is the publicly funded universal health care insurance scheme in Australia that fully or partly covers treatments and services provided by health practitioners.

##### Anthropometrics

Height (stadiometer) and weight (electronic scales) will be measured at weeks 0, 12 and 24. BMI will be calculated as weight/height^2^. During Telehealth appointments, height and weight will be self-reported if possible.

##### X-ray

The degree of X-ray damage may be an effect modifier. A standing anteroposterior semi-flexed x-ray of the study knee will be performed at screening for classification purposes. X-rays will be scored for joint space narrowing and osteophytes on a four-point scale (0–3) using the OARSI atlas [34, 35]. This method has very high reproducibility with an ICC of 0.98 for joint space narrowing and 0.99 for osteophytes [50].

##### PainDETECT

The painDETECT questionnaire assesses to what degree a participant’s pain is neuropathic like [51]. This may be an effect modifier and will be measured at weeks 0, 12 and 24.

##### Depression

Depression may be an effect modifier. It will be assessed using the Patient Health Questionnaire (PHQ-9) [52] at weeks 0, 12 and 24.

##### Fibromyalgia-ness

We will use the Symptom Impact Questionnaire (SIQR) to assess patients’ symptoms of fibromyalgia which is a validated questionnaire to assess fibromyalgia-ness in non-fibromyalgia patients [53, 54]. This will be assessed at weeks 0, 12 and 24.

### Safety

The risks associated with diacerein use have been well-documented [24]. Adverse events (AEs) will be monitored throughout the study. Standard safety and efficacy monitoring will be performed through regular face-to-face visits and/or Telehealth appointments and/or phone calls between visits. The patients are requested to report any AE to the research staff spontaneously. Details of the AE and its relationship with study intervention will be recorded and reported to the Ethics Committees. We will code all the AEs according to the Medical Dictionary for Regulatory Activities (MedDRA).

### Sample size calculations

#### Pain (primary outcome)

Based on in-house data from the 4Jointz trial [45], 234 participants will give us 90% power, with 5% probability of type 1 error (alpha=0.05) to detect a 10mm difference between diacerein and placebo on the VAS pain scale (standard deviation (SD) of pain change 25.5 in the placebo group and 21.5 in drug group). To allow for a 10% loss to follow-up, we need 260 participants (130 in each arm). We expect to see a larger effect than published in the diacerein meta-analysis (8.7mm) [20] due to targeting the therapy for those with effusion-synovitis. We will have >99% power to detect a difference of 15 mm, the minimum clinically important difference (MCID), on a 100mm VAS for OA trials [39].

